## Abstract

**Introduction:**

Pectus excavatum repair is associated with substantial postoperative pain, despite the use of epidural analgesia and other analgesic regimens. Perioperative recorded music interventions have been shown to alleviate pain and anxiety in adults, but evidence for children and adolescents is still lacking. This study protocol describes a randomised controlled trial that evaluates the effects of recorded music interventions on postoperative pain relief in children and adolescents after pectus excavatum repair.

**Methods:**

A multicentre randomised controlled trial was set up comparing the effects of perioperative recorded music interventions in addition to standard care with those of standard care only in patients undergoing a Nuss procedure for pectus excavatum repair. One hundred and seventy subjects (12–18 years of age) will be included in three centres in the Netherlands. Patient inclusion has started in November 2018, and is ongoing. The primary outcome is self-reported perceived pain measured on the visual analogue scale. Secondary outcomes are anxiety level, analgesics consumption, vital parameters such as heart rate, blood pressure and respiratory rate, length of hospital stay, postoperative complications, quality of life and cost-effectiveness.

**Ethics and dissemination:**

This study is being conducted in accordance with the Declaration of Helsinki. The Medical Ethics Review Board of Erasmus University Medical Centre Rotterdam, The Netherlands, has approved this protocol. Results will be disseminated via peer-reviewed scientific journals and conference presentations.

**Trial registration number:**

NL6863

Strengths and limitations of this studyThis study is the first multicentre randomised controlled trial evaluating the effects of recorded music interventions on pain experience in older children before, during and after pectus excavatum repair with the Nuss procedure.Data will be collected during hospitalisation and up until 3 months postoperatively to shed light on the effect of perioperative recorded music interventions during hospitalisation and after hospitalisation evaluating both short-term and potentially long-term effects.The study participants and participating surgeons are not blinded to the interventions, which is a limitation; however, the anaesthesiologists and pain specialists will be blinded to the study arm allocation.

## Introduction

Pectus excavatum (PE) is the most common congenital chest wall deformity affecting 0.1%–0.8% of live births, affecting boys more than girls. Operative repair is indicated when symptoms or signs of heart and/or lung dysfunction are present,^1^ or when the patient is much concerned about the cosmetic appearance and psychosocial problems occur.^2 3^ The optimal age for repair is between 12 and 16 years.^4^ Numerous surgical techniques have been developed to correct PE, of which the Nuss procedure is now among the most commonly employed techniques.^5 6^ The Nuss procedure involves inserting a convex steel bar beneath the sternum to reposition the sternum anteriorly and thereby effectively correcting the deformity.^7^ It is associated, however, with substantial postoperative pain, despite the use of epidural analgesia or patient-controlled intravenous opioid administration.^8 9^ Pain management is the critical component of postoperative care as postoperative pain has implications for activity and quality of life^10^ and is the primary factor determining the length of hospital stay.^11^

Therefore, interest is growing in finding new ways to alleviate postoperative pain, such as perioperative music interventions. In previous studies in adult surgical patients, recorded music interventions reduce pain medication consumption and improve the management of pain and anxiety.^12–20^ However, in children and adolescents undergoing surgery, a definite conclusion about the effect of recorded music interventions has yet to be drawn.^21^ Especially in paediatric surgical procedures associated with substantial postoperative pain, such as the Nuss procedure, music interventions might be effective in reducing children’s pain and anxiety. We designed a multicentre randomised controlled trial (Interventions with Music in PECTus excavatum treatment (IMPECT) trial) to evaluate whether adjuvant recorded music interventions are indeed associated with less postoperative pain in children and adolescents undergoing the Nuss procedure for PE repair.

## Methods and analysis

### Study design

The IMPECT trial is a randomised controlled trial with two study arms, designed to compare the effects on postoperative pain of perioperative recorded music interventions in addition to standard care (intervention group) versus standard care (control group)—prior, during and after the Nuss procedure for PE repair. We will include 170 subjects of children and adolescents (12–18 years of age) operated on in three centres in the Netherlands: the Erasmus University Medical Centre-Sophia Children’s Hospital, Rotterdam; Haga Hospital-Juliana Children’s Hospital, The Hague; and Academic Medical Centre-Emma Children’s Hospital, Amsterdam. We started enrolment in November 2018. The first patient included was in January 2019. This study protocol follows the Standard Protocol Items: Recommendations for Interventional Trials (SPIRIT) guidelines (see SPIRIT checklist in online supplementary material). The underlying protocol follows the Consolidated Standards of Reporting Trials (CONSORT) guidelines for non-pharmacological treatments. This trial was registered on trialregister.nl.

10.1136/bmjopen-2019-036380.supp1Supplementary data

### Randomisation, blinding and treatment allocation

A parallel randomisation with equal allocation ratio is being carried out to individually allocate subjects to either the intervention or the control group. An online web-based randomisation program (ALEA; FormVision, Abcoude, The Netherlands) generates the random allocation sequence by the use of random block size randomisation and is stratified by centre with an equal allocation ratio per centre in both study arms. Allocation concealment will be ensured, as the service will not release the randomisation code until the patient has been recruited into the trial. The anaesthesiologists and pain specialists involved do not have access to the randomisation program and are blinded to the subject’s study arm allocation, as well as the person analysing the data.

### Interventions

Subjects in the intervention arm receive a recorded music intervention prior to and during surgery and postoperatively the first 3 days (see figure 1). The music intervention prior to surgery is 30 min long and takes place before the administration of premedication. After induction of general anaesthesia and after final positioning of the patient a headphone with music is applied and will remain during surgery. The headphones will be removed at the recovery unit, when patients are fully awake. The music interventions after surgery are each 30 min long and take place twice a day, in the morning and evening. In each hospital, the best times to start the intervention will be established to assure blinding of both the anaesthesiologists and pain specialists. Subjects in the control arm rest for 30 min prior to surgery and the administration of premedication, and wear a headphone without music during surgery. After surgery, they receive regular postoperative care without music interventions. Subjects in the control group are instructed to refrain from much listening to music during the hospital stay. The subjects in both control group and intervention group are requested to self-document all activities performed, such as listening to music, playing video games, using the computer and watching movies and television. Participation ends at the scheduled postoperative check-up at the outpatient clinic (see figure 1). All study measurements take place during hospitalisation and at the outpatient clinic. No extra visits to the hospital are required.

**Figure 1 F1:**
[figure not shown]
Flow chart of study interventions and assessments.

### Music selection

It has been suggested that individual music preference is important to the effect of a music intervention.^22^ Nevertheless, a study has shown that playing music from a preselected playlist by the researcher has the largest beneficial effect on postoperative pain, compared with the subject’s own favourite music or preselected music without taking the music preference of the subject into account.^19^ However, definite conclusions in this regard cannot be drawn. Furthermore, research in rodents suggests that loud rock music may have a negative effect and may act as a stressor.^23^

Therefore, in collaboration with a specialised music therapist we have composed three music playlists without loud rock music, which the subject can choose from. The playlists are categorised into three different genres of music: pop, lounge and classical music. Subjects can choose from either of these playlists. Subjects may choose a different playlist during surgery. Music will be heard through an on-ear headphone connected to a digital music player. After surgery, subjects in the intervention group may listen to their own preferred music. Approval from Buma/Stemra, the Dutch collecting society for composers and music publishers, has been received to use any licensed music.

### Anaesthetic treatment

There is no nationwide standard anaesthesia protocol for the Nuss procedure in the Netherlands. Therefore anaesthesia protocols differ between centres. Randomisation should control for such variation between centres. However, it will be analysed statistically.

All centres apply EMLA cream at the intravenous line insertion site. Furthermore, all patients receive epidural analgesia, which are preferably placed at fifth thoracic level. All centres used long-acting local anaesthetics with an adjuvant epidurally. General anaesthesia was induced and maintained by propofol combined with opioids and neuromuscular relaxation induced by rocuronium. Postoperative analgesia was maintained with a continuous epidural infusion of a long-acting local anaesthetic (ropivacaine 0.2% or bupivacaine 0.125%) with an adjuvant. All patients received weight-based doses of paracetamol and a non-steroidal anti-inflammatory drug postoperatively. After epidural removal pain was treated by oral opioids as required.

However, there are some major differences between hospitals: the Emma Children’s Hospital gives standard premedication with clonidine 150 μg and 300 mg gabapentin, while the other two hospitals do not give any pharmacological premedication. Furthermore, in Emma Children’s Hospital patients receive gabapentin 300 mg twice daily for 5 days and receive patient-controlled analgesia with morphine in addition to the epidural catheters. Finally, while Juliana and Sophia Children’s Hospitals use sufentanil 0.5 μg/mL as an epidural adjuvant, Emma Children’s Hospital uses clonidine 1 μg/mL.

### Outcome parameters

The primary outcome parameter is pain, defined as the average pain score, as measured by a visual analogue scale (VAS-pain), that patients will report at the third day postoperatively. The scale of the VAS-pain varies from 0 to 100, whereas 0 is defined as no pain and 100 as the worst pain imaginable. This scale has been recommended and validated for the measurement of acute pain in children 8 years of age and above and is also sensitive to changes in pain levels postoperatively.^24–26^

Secondary outcome parameters include:

The morphine consumption in the first 3 days postoperative as calculated by the morphine equivalent daily dose/kilogram (MEDD/kg) and the consumption of other analgesics in milligrams.Physiological variables such as heart rate, blood pressure and respiratory rate will be measured throughout their hospital stay.Levels of anxiety and distress will be measured before surgery through the State-Trait Anxiety Inventory (STAI) for children. This questionnaire consists of two separate 20-item self-report rating scales for measuring trait and state anxiety. The trait anxiety is a relatively stable personality disposition, while state anxiety is the situation-related anxiety and this may differ depending on the stress of a particular moment.^27^ The questionnaire has been translated into Dutch and has been validated.^28^Quality of life will be measured before surgery and at their first check-up at the outpatient clinic through the Child Health Utility Questionnaire (CHU9D). This validated questionnaire consists of nine items that assess the child’s functioning across domains of worry, sadness, pain, tiredness, annoyance, schoolwork/homework, sleep, problems with daily routine and ability to join in activities.^29–31^Postoperative complications and length of hospital stay are recorded.The subject’s postprocedural pain after 3 months will be evaluated with the VAS, the CHU9D and the ‘TNO questionnaire for sport and physical activity’. This validated Dutch questionnaire assessed a person’s daily activities.^32^ This questionnaire serves to measure rehabilitation as a derivative of the postprocedural pain. Baseline measurements for the ‘TNO questionnaire for sport and physical activity’ will also be performed before surgery.Considering the potential influence of pain and the use of analgesics on length of stay, cost-effectiveness of the intervention will be determined through a cost-utility analysis.

### Eligibility criteria

Potential subjects visiting the outpatient clinic of the three paediatric surgery departments involved will be informed about our study. A member of the research team undertakes the initial screening for eligibility. The following inclusion criteria apply:

Ages 12–18 years.Scheduled for primary PE repair according to the Nuss procedure with either one or multiple bars.Postoperatively, initial placement of a thoracic epidural or both thoracic epidural and patient-controlled analgesia system.Good knowledge of the Dutch language, by both patients and parents.Written informed consent. Additional written informed consent by parents or legal guardian is only necessary for children under the age of 16 years.

The following exclusion criteria apply:

Hearing impairment.Secondary PE surgery or other prior thoracic surgery.Known severe mental or psychiatric disorder.Known impaired communication with patient and parents as collected.Presence of chronic pain syndrome: ongoing pain lasting longer than 3 months or ongoing pain lasting longer than the reasonably expected healing time for the involved tissues.

One week after being informed about the study, eligible subjects will be called by telephone to inquire if they wish to participate.

### Sample size

A power calculation was performed by the Department of Biostatistics of the Erasmus Medical Centre for the primary outcome parameter: pain, defined as the average pain score, as measured by a VAS, that patients will report at the third day postoperatively. Evidence on the effects of recorded music interventions prior, during and after surgery in PE repair is lacking. However, a recent meta-analysis, which investigated music interventions on pain in surgical patients, found an overall effect size measured as the Cohen’s delta of −0.50 (95% CI −0.66 to −0.34).^19^

We assumed a low correlation between the VAS score preoperatively and postoperatively of 0.3. Thus, to obtain a power of 90% using a two-sided significance level of p<0.05, each study arm requires 77 subjects. To account for dropouts, we will include 85 subjects per study arm, resulting in a total sample size of 170.

### Statistical analysis

The main study endpoint will be the VAS-pain score reported by the subject during the length of hospital stay, three times a day. The mean VAS-pain score of each day will be calculated per subject. The mean VAS-pain scores between the music and control group on the third day will be compared with an analysis of covariance (ANCOVA) test, with adjustment for the effects of centre and baseline VAS-pain score. The main analysis will be based on the intention-to-treat principle. In case of non-compliance, a sensitivity analysis will be performed using per-protocol analyses. A two-sided p value <0.05 will be considered to be statistically significant. For the primary outcome parameter, only the available data will be analysed (no imputation of missing data).

In a sensitivity analysis, we will also adjust for possible confounder variables in the linear regression model for the following variables: age, gender, body mass index and epidural use. Finally, we will also perform a second sensitivity analysis to determine if the effectiveness of the intervention depends on the type of music chosen, by adding these genres as categories to the linear regression model.

The VAS score of each time point will be analysed using a linear mixed model, with the baseline value (observed before surgery), group (control arm or intervention arm), centre and time point, and the interaction between group and time point as independent variables. Total consumption of analgesics and type of analgesics in milligrams will be added to the analyses. Also an interaction effect of centre and group will be examined due to variation in anaesthesia protocols in the participating centres. Using information criteria, it will be determined if it is necessary to add a random intercept and/or random slope of time point to this model, to account for the within-subject correlations. If required, a transformation of the outcome will be applied to ensure normality of the model residuals.

The secondary outcome parameters will be analysed as follows:

MEDD/kg and total dosage of other analgesia.

There may be differences between centres in usage of patient-controlled analgesia and epidural anaesthesia. Therefore, the difference between the intervention group and the control group will be tested using multiple linear regression, with adjustment for the effects of centre. When necessary, an appropriate transformation of the outcome (MEDD/kg) or total dosage of other analgesia in milligrams will be performed to achieve a normal distribution of the residuals.

Score on STAI questionnaire and health-related quality of life (HRQoL).

The scores of the STAI and HRQoL questionnaires will be compared between groups using ANCOVA, with group, centre and the baseline STAI score and HRQoL score before the intervention or the resting period as independent variables.

Physiological measurements, including blood pressure, heart rate and respiratory rate.

These variables will be analysed using a linear mixed model, with the baseline value (observed before surgery), group (control arm or intervention arm), centre, time point, and the interaction between group and time point as independent variables.

Using information criteria, it will be determined if it is necessary to add to a random intercept and/or random slope of time point to this model, to account for the within-subject correlations. If necessary, a transformation of the outcome will be applied to ensure normality of the model residuals.

Complications, like postoperative ileus (number of days), nausea/vomiting (number of days and also antiemetics used) and pruritus.

The duration of postoperative ileus, nausea and vomiting will be compared between groups using a Mann-Whitney test, stratified by centre (ie, a Van Elteren test). The percentage of patients with pruritus will be compared between groups using a stratified χ^2^ test.

Length of hospital stay (number of days).

The length of hospital stay will be compared between groups using a Mann-Whitney test, stratified by centre (ie, a Van Elteren test).

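### The music-genre sensitivity analysis cannot show that effectiveness depends on genre: genre is self-selected and exists only in the music arm

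*Protocol article*

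**What the plan says.** The Statistical analysis section adds a second sensitivity analysis to the day-3 ANCOVA. Its purpose and method stand in one sentence, which asks "if the effectiveness of the intervention depends on the type of music chosen, by adding these genres as categories to the linear regression model". No interaction term is named, and no coding is given for subjects without a genre.

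Under Music selection, "The playlists are categorised into three different genres of music: pop, lounge and classical music". The choice is the subject's: "Subjects can choose from either of these playlists". It need not stay fixed: "Subjects may choose a different playlist during surgery". Nor need it stay within the three categories: "After surgery, subjects in the intervention group may listen to their own preferred music".

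Under Interventions, controls rest before surgery and "wear a headphone without music during surgery". For the days that follow, "After surgery, they receive regular postoperative care without music interventions". Nothing in the article says that controls name a preferred playlist.

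**The concern.** Whether effectiveness depends on genre is a question of effect modification: is the music-versus-control difference larger for one kind of music than for another? Answering it needs, for each genre, a control group comparable with the subjects who chose that genre. The plan as described has none. Its genre terms compare pop, lounge and classical choosers with one another, or each of them with all controls.

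Those groups are not randomised. If classical choosers differ from pop choosers in anything that affects day-3 pain, such as anxiety, the difference appears as a genre effect. It can also run the other way and hide a real one. The Music selection section itself calls the evidence on choice of music inconclusive, so readers may use this result to decide which music to offer.

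**Working it through.** **Inputs from the protocol article.** Sample size section: Cohen's d 0.50 in absolute value, pre/post correlation 0.3, 90% power, two-sided 5%, 77 per arm. Music selection: three genres. Statistical analysis: ANCOVA with group, centre and baseline VAS. The article gives no genre split, no genre effects and no prognostic strength of preference. Every such value below is an assumption.

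**1. The plan's own figure.** n per arm = 2(1.960 + 1.282)² × (1 − 0.3²) / 0.5² = 84.06 × 0.91 = 76.5, rounded up to 77. The stated size reproduces, so its SD scale and residual SD of √0.91 are used in steps 3 and 4.

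**2. Can the genre terms be estimated?** Columns: intercept 1, group 1, genre indicators 3, centre 2, baseline 1, which makes 8. The three genre indicators sum to the group indicator, so the rank is 7. With group plus two genre indicators, or one four-level factor (control, pop, lounge, classical), there are 7 columns of rank 7. The redundancy is a matter of coding, and two between-genre contrasts remain estimable.

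**3. What does the 2-df genre test measure?** Simulation of 3,000 trials per scenario, 77 per arm, preferences equally likely, three centres without a centre effect. The last column is the test of group by preference when preference is known in both arms.

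| Prognostic shift by preference (SD) | Music effect by genre (SD) | Mean contrast, extreme genres (SD) | Genre test as planned rejects | Group × preference rejects |
|---|---|---|---|---|
| 0 / 0 / 0 | −0.5 in each | 0.00 | 5.2% | 4.8% |
| +0.25 / 0 / −0.25 | −0.5 in each | −0.50 | 34% | 4.8% |
| +0.40 / 0 / −0.40 | −0.5 in each | −0.80 | 73% | 4.8% |
| 0 / 0 / 0 | −0.25 / −0.5 / −0.75 | −0.50 | 36% | 19% |
| −0.5 / 0 / +0.5 | 0 / −0.5 / −1.0 | 0.00 | 4% | 63% |

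Rows 2 and 4 carry the point. A prognostic preference with no effect modification, and true effect modification with no prognostic preference, give the same mean contrast and nearly the same rejection rate. The planned test cannot tell them apart. In row 5 a true genre difference of 1.0 SD is hidden.

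**4. Power of the planned test, taken at face value.** With effects of −0.75 / −0.50 / −0.25 SD and no confounding, the noncentral F (2 and 147 df) gives 36% for a 26/26/25 split of the music arm, 25% for 50/20/7 and 20% for 60/12/5.

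**5. Precision of the interaction.** With an assumed 60/20/20 split of 77, the pop-versus-lounge contrast within one arm has SE = √(1/46.2 + 1/15.4) = 0.294 SD. Differencing it between two arms gives 0.294 × √2 = 0.42 SD. By the same formula, an even split gives √(2/25.67) × √2 = 0.39 SD and 80/10/10 gives √(1/61.6 + 1/7.7) × √2 = 0.54 SD. These SEs leave out the baseline adjustment, which would multiply them by √0.91 = 0.95.

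**6. Does the category match the outcome?** Two sessions a day for three days make six scheduled postoperative sessions. In any of them the subject may play own music, while the outcome is the day-3 mean VAS. The sessions nearest the outcome may therefore fall outside the three genres.

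**The case against.** - **A reader might infer that the model cannot be fitted because genre is collinear with group.** The article does not support that. It says only that genres enter as categories, and ordinary factor coding gives full rank (step 2). When preference is not prognostic, the test even has the right size, 5.2%.
- **The comparison may not be unadjusted.** The sentence before describes a linear regression with age, gender, body mass index and epidural use, and the genres may well be added to that model. This would remove confounding by those variables. Anxiety and other unmeasured differences between choosers would remain.
- **A reader might infer that genre is chosen after allocation.** The article does not say when the choice is made. A condensed article might also omit a form item on which controls state a preference. If such an item exists, the data for a proper test are at hand, but adding genre as categories alone would give a main effect of preference and still not the interaction.
- **Exposure is partly recorded.** Under Interventions, both arms are asked to keep a record of activities that includes music listening. Whether it captures genre is not stated.
- **It is only a sensitivity analysis.** This is correct and limits the severity. That a difference would be reported as a genre effect is a risk, not something the article states.

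**Conclusion.** The point holds in this form: the planned genre analysis cannot validly show that the effectiveness of music depends on genre. The obstacle is self-selection without a control counterpart for each genre, made worse by a category that may change at surgery and lapse afterwards. Collinearity is not the obstacle.

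Under an assumed prognostic preference of ±0.25 to ±0.40 SD, equal preference shares and the same music effect in every genre, the false-positive rate is about 34% to 73% against a nominal 5%. If preference carries no prognostic information, the inflation disappears; the article gives no means of knowing which applies. Severity is minor: the primary ANCOVA, the sample size and the secondary endpoints are untouched.

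**What to change.** For subjects still to be enrolled, ask both arms for their preferred playlist before randomisation. Fit group + preferred genre + group × preferred genre, with centre and baseline VAS. Report the interaction as exploratory, and state that it tests effect modification by preference, not by the genre actually played.

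For subjects already enrolled without that item, or for the whole trial if recruitment is too far advanced, report genre results descriptively within the music arm and remove the aim of showing that effectiveness depends on genre.

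The cost is one baseline question, one model line and a short change of wording. The interaction will be imprecise: an SE of about 0.42 SD for pop versus lounge under the 60/20/20 assumption with 77 per arm, and larger if only later subjects contribute. A null result would therefore say little.

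### The VAS mixed model adjusts for analgesic consumption, a post-randomisation outcome, so its group and group-by-time terms do not estimate the total effect of music on pain

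*Protocol article*

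**What the plan says.** All references are to the protocol article.

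- **Primary analysis** (Statistical analysis). Mean VAS on the third day is compared by ANCOVA, "with adjustment for the effects of centre and baseline VAS-pain score".
- **Repeated-measures analysis** (same section). "The VAS score of each time point will be analysed using a linear mixed model, with the baseline value (observed before surgery), group", followed by centre, time point and the group-by-time interaction. The next sentence is "Total consumption of analgesics and type of analgesics in milligrams will be added to the analyses", and after it comes a further model term, centre by group. The sentence on analgesics carries no sensitivity, exploratory or mediation label.
- **Consumption as an outcome** (Outcome parameters; Statistical analysis). Morphine equivalents per kilogram over the first three postoperative days, and milligrams of other analgesics, are secondary outcomes. They are compared between arms by linear regression adjusted for centre.
- **Earlier evidence** (Introduction). In adult surgical patients, "recorded music interventions reduce pain medication consumption". For children and adolescents the Introduction says that no definite conclusion has been reached.
- **Dosing** (Anaesthetic treatment). Part follows a fixed scheme: epidural infusion, weight-based paracetamol and an anti-inflammatory drug, and gabapentin in one centre. Part is driven by the patient's pain: patient-controlled morphine in one centre, and oral opioids as needed once the epidural is out.
- **Sensitivity model** (Statistical analysis). The added covariates are "age, gender, body mass index and epidural use". Under Anaesthetic treatment, "all patients receive epidural analgesia".

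**The concern.** Randomisation makes the arms comparable at baseline. It does not make patients with equal later consumption comparable across arms. If music lowers pain, and patients in less pain ask for less medication, then comparing arms at equal consumption removes part of the effect under study. It also opens a non-randomised path through whatever else drives both pain and dosing. A music patient who used as much opioid as a control patient is likely to have had more underlying pain for other reasons.

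The covariate is moreover described as a total. Read literally, an early VAS reading would be adjusted for doses given after it.

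At stake is the only planned analysis of VAS at the individual time points, which the Statistical analysis section opens by describing as recorded three times a day throughout the stay. Beside an unbiased day-3 result it could show a shrunken effect, an enlarged one, or one that does not exist.

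**Working it through.** **1. The plan's own figure.** Inputs from Sample size: d = 0.50, correlation 0.3, power 90%, two-sided 0.05.

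n per arm = 2(1.960 + 1.282)² / 0.50² × (1 − 0.3²) = 84.06 × 0.91 = 76.49, rounded up to 77. The stated 77 reproduces, with power 90.2%. It belongs to the ANCOVA and does not change with the fix.

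**2. A model for the bias.** The protocol gives no association between pain and consumption, so g, δ and k below are assumptions. T is arm, B is baseline and L is underlying pain.

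- L = −0.5T + 0.3B + e, with var(e) = 0.91
- Consumption A = gL + δT + u, with var(u) = 1 − g²
- VAS = L − kA

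Here g is how strongly consumption follows pain, δ is any further effect of music on consumption, and k is the pain relief per unit of consumption. Let λ = 0.91g / (0.91g² + 1 − g²), the slope of L on A given arm and baseline.

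- Total effect = −0.5(1 − kg) − kδ
- Effect adjusted for A = −0.5(1 − λg) − λδ
- Difference (adjusted − total) = (λ − k)(0.5g − δ)

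The second bracket is the fall in consumption that music causes. The bias vanishes only if music leaves consumption unchanged or if λ happens to equal k. In this model the direct effect at fixed consumption is −0.5, and the adjusted coefficient does not recover that either.

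**3. Numbers.** λ = 0.275, 0.466 and 0.773 for g = 0.3, 0.5 and 0.8. Ratio of adjusted to total effect:

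| g | k | δ = 0 | δ = −0.2 |
|---|---|---|---|
| 0.3 | 0 | 0.92 | 0.81 |
| 0.3 | 0.2 | 0.98 | 0.94 |
| 0.3 | 0.4 | 1.04 | 1.12 |
| 0.5 | 0 | 0.77 | 0.58 |
| 0.5 | 0.2 | 0.85 | 0.71 |
| 0.5 | 0.4 | 0.96 | 0.91 |
| 0.8 | 0 | 0.38 | 0.07 |
| 0.8 | 0.2 | 0.45 | 0.10 |
| 0.8 | 0.4 | 0.56 | 0.14 |

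The formulas agree with a simulation of 1,000,000 patients at a single time point. The effect is attenuated in 16 of 18 settings and overstated in two.

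**4. Outside the grid.** In a second model, L = −0.5T + U with var(U) = 1, A = 0.8L + e₁ (SD 0.8) and VAS = L − kA + e₂ (SD 0.6). Pain then explains 0.64 / (0.64 + 0.64) = 0.5 of consumption within arm. The adjusted effect is −0.5(1 − 0.5) = −0.25 whatever k is. The total effect −0.5(1 − 0.8k) is −0.42, −0.30 and −0.10 for k = 0.2, 0.5 and 1.0. At k = 1.0 the adjusted figure is 2.5 times the total.

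**5. A nil effect.** Let music leave pain unchanged and lower consumption by 0.5 units (0.44 SD), with k = 0. Then λ = 0.8 / 1.28 = 0.625, and the adjusted effect is 0.625 × 0.5 = +0.31, against music, although the true effect is 0. With 77 per arm the standard error is 0.153 and z = 2.04. About 52% of trials would be significant, against about 5% without the covariate.

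**The case against.** Several objections have force.

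*The primary analysis is sound.* This stands. A reader might infer that the trial's main result is biased, or that the plural in the sentence on analgesics reaches the ANCOVA. The protocol does not support this: the ANCOVA has its own covariate list, and the sentence sits among the mixed-model terms.

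*The wording is loose.* It does not say whether the adjusted model replaces or accompanies an unadjusted one, and the full protocol may say more. That is true, but its place among the model terms makes covariate adjustment the natural reading.

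*The large figures rest on strong assumptions.* This also stands. The 52% requires analgesics to have no effect on VAS. In that setting with k = 0.5, the true effect is +0.25 against an adjusted +0.31, so it is no longer a null; at k = 0.625 the bias is zero. If pain explains only 10% of consumption (slope 0.267, k = 0), the adjusted effect is 0.375 × 0.5 = 0.19, z is 0.99, and rejection falls to about 17%. Much of the dosing is fixed by scheme, which favours the weaker associations.

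*The Introduction does not predict lower consumption in this trial.* Correct. It reports adult studies and leaves the question open for this age group. The point needs only that an effect on consumption is possible, and the plan itself tests for one.

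*Epidural use need not share the fault.* It is undefined and appears only in a labelled sensitivity analysis. A reader might infer the same bias there. That would follow only if it meant duration or dose after allocation; a regimen fixed by centre would be harmless.

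**Conclusion.** The point holds for the VAS mixed model, at moderate severity. With analgesic consumption as a covariate, the group and group-by-time coefficients are not the total effect of music on pain. They are not an identified direct effect either, because no estimand is stated and nothing removes the shared causes of pain and dosing.

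This rests on two conditions that the protocol makes plausible: consumption follows pain in part, and music may change it. The size and sign of the bias cannot be fixed from the protocol. The range of 0.07 to 1.12 times the total effect belongs to the assumed grid and is not a forecast; a stronger analgesic effect falls outside it. Attenuation is the commoner result there. Neither a false-positive rate near one half nor a reversed sign can be claimed as an expected outcome.

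Differences between centres in anaesthetic practice do not call for the adjustment. Randomisation is stratified by centre, centre is in the model, and the centre-by-group interaction is to be examined.

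**What to change.** 1. Specify the main VAS mixed model with baseline VAS, centre, group, time point and group by time, and remove analgesic consumption and type from it. The separately planned look at centre by group can stay.
2. Report MEDD/kg and other analgesics as outcomes in their own right, as the plan already provides, and read them beside the VAS result.
3. If a consumption-adjusted model is still wanted, label it exploratory or a mediation analysis, state its estimand and assumptions, and present it beside the main model.
4. In the sensitivity model, define epidural use as a characteristic fixed before randomisation, or drop it. Every eligible patient starts with an epidural, so a yes/no term for initial placement is constant, while duration or dose arises after randomisation.

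A combined score of pain and consumption is optional and not part of this fix.

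The cost is a few sentences of analysis text, settled before unblinded data are analysed. No new data are needed, and the 77 per arm is unchanged.
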